## Abstract

**Background:**

Considering the high costs of sick leave and the consequences of sick leave for employees, an early return-to-work of employees with mental disorders is very important. Therefore, a workplace intervention is developed based on a successful return-to-work intervention for employees with low back pain. The objective of this paper is to present the design of a randomized controlled trial evaluating the cost-effectiveness of the workplace intervention compared with usual care for sick-listed employees with common mental disorders.

**Methods:**

The study is designed as a randomized controlled trial with a follow-up of one year. Employees eligible for this study are on sick leave for 2 to 8 weeks with common mental disorders. The workplace intervention will be compared with usual care. The workplace intervention is a stepwise approach that aims to reach consensus about a return-to-work plan by active participation and strong commitment of both the sick-listed employee and the supervisor. Outcomes will be assessed at baseline, 3, 6, 9 and 12 months. The primary outcome of this study is lasting return-to-work, which will be acquired from continuous registration systems of the companies after the follow-up. Secondary outcomes are total number of days of sick leave during the follow-up, severity of common mental disorders, coping style, job content, and attitude, social influence, and self-efficacy determinants. Cost-effectiveness will be evaluated from the societal perspective. A process evaluation will also be conducted.

**Discussion:**

Return-to-work is difficult to discuss in the workplace for sick-listed employees with mental disorders and their supervisors. Therefore, this intervention offers a unique opportunity for the sick-listed employee and the supervisor to discuss barriers for return-to-work. Results of this study will possibly contribute to improvement of disability management for sick-listed employees with common mental disorders. Results will become available in 2009.

**Trial registration:**

ISRCTN92307123

## Background

### CMDs and sick leave

Common mental disorders (CMDs) are common in the community and often affect functioning to such an extent that they are associated with work absenteeism. In many developed countries, 35% to 45% of absenteeism from work is due to mental health problems [1]. Prolonged absence from work often results in a lack of social structure and meaningful activity[2,3] and is associated with a reduced probability of eventual return-to-work (RTW) and an increased probability of subsequent economic and social deprivation [4,5]. In the beginning of the sick leave episode the employee is often missed at work and employers will try to facilitate RTW. However, if sick leave continues, the employee will be replaced and the balance will be regained without the sick-listed employee and therefore RTW will become increasingly difficult to accomplish [6,7]. Thus, work itself can be an important factor in the RTW process[2]. It is also known that work is a significant contributor to the quality of life [8]. Considering the high costs of sick leave and the adverse consequences of sick leave for employees, an early RTW is very important.

### A workplace intervention for CMDs

A recent publication describes the structured development, implementation and planning for the evaluation of a return-to-work (RTW) intervention for sick-listed employees with common mental disorders (CMDs)[9]. The intervention is based on an existing successful RTW intervention for sick-listed employees with low back pain[10,11]. Until now, for mental health problems the focus of interventions is mainly on the reduction of symptoms, while for musculoskeletal disorders the focus has shifted to the prevention of long-term work disability [12]. The main goal of the intervention for employees with low back pain was the facilitation of RTW[10]. Therefore, employees and their supervisors discussed about barriers for RTW and solutions, and they drew up a plan for implementation of solutions which is based on consensus between the employee and the supervisor.

In the development of such an intervention for sick-listed employees with CMDs the steps of Intervention Mapping were followed[13]. In this, important stakeholders in the process of RTW (i.e. employees recently sick-listed with CMDs, supervisors and occupational health professionals) participated in focus group interviews. Topics like, equality and support in discussions about RTW, the role of an RTW coordinator and the suitable moment to apply this workplace intervention for sick-listed employees were discussed. This resulted in a structured return-to-work intervention, specifically tailored to the needs of sick-listed employees with CMDs [9].

### Objective

The objective of this paper is to describe the design of a cost-effectiveness study of the workplace intervention for sick-listed employees with CMDs. This intervention will be compared with usual care.

## Methods

In order to describe the design of this study we followed the CONSORT statement[14,15], a checklist that intends to improve the quality of reports of randomised controlled trials.

### Organisation study

The study is designed as a randomised controlled trial with a follow-up of one year. The design is presented in Figure 1. Two occupational health services in the Netherlands collaborate in the study, one occupational health service belongs to the VU University and the VU University Medical Center, and the other is attached to CORUS, a steel industry company.

**Figure 1 F1:**
[figure not shown]
Study design.

The Medical Ethics Committee of VU University Medical Center approved the study design, protocols, procedures and informed consent. Participation is voluntary and all participants signed informed consent. Towards the involved stakeholders (employees, supervisors and occupational health professionals) the study is entitled the "ADAPT" study.

### Participants

The source population (n ≈ 20.000) consists of blue and white collar employees working in the University, the University Medical Center and the steel factory. The source population is diverse: the healthcare sector, the industrial sector and administrative sector are all involved in this study. The workplace intervention is assumed to be appropriate for all these sectors.

The employees eligible for this study are on sick leave from regular work for 2 to 8 weeks with CMDs. CMDs encompass both criteria-based psychiatric disorders (mostly depressive and anxiety disorders) and 'subthreshold' disorders (including adjustment disorders)[16]. Employees with CMDs are selected on the basis of elevated distress levels and sick leave. Distress reflects the effort people have to put into coping with stressors in order to maintain their habitual level of psychosocial functioning[17]. Severe distress, however, may lead to a breakdown in coping, resulting in psychosocial disfunctioning (e.g. sick leave). It is generally known that distress and depression coexist with chronic diseases and/or physical symptoms [18-21], therefore a heterogeneous group of participants will be selected.

Employees are in the working age range, 18 to 65 years old. Exclusion of employees occurs in case of 1) a conflict between the employee and the employer with legal involvement; 2) working less than 12 hours a week; 3) pregnancy; 4) sick-listed for more than 8 weeks; 5) another episode of sick leave within one month before the current episode; 6) inability to complete questionnaires written in the Dutch language. After randomisation the occupational physician (OP) is responsible to prevent employees with severe psychiatric disorders (mania, psychosis or suicidal) and employees with a terminal illness from starting the workplace intervention.

### Recruitment of study population

All employees sick-listed for more than one week are selected from the databases of the occupational health services and they are sent a letter from their OP with a screening questionnaire. In the letter, the OP requests the employee to fill in the screening questionnaire and to send it back to the researcher. The screening questionnaire contains three questions based on the distress scale of the Four-Dimensional Symptom Questionnaire (4DSQ) [17,22,23] and a question about whether or not the employee is sick-listed. A screening distress score ≥ 4 corresponds with a 4DSQ distress score ≥ 11, the optimal cut-off for any psychosocial problem [23]. The screening procedure allows the researchers to approach the sick-listed employees in an early stage of sick leave, when other treatments have not yet or only just started, and before the 8 weeks RTW plan is started which is obligated according to the Improved Gatekeeper Act.

Employees who return the questionnaire, meet the distress and sick leave criteria and who indicate 'willing to participate' are contacted by the researchers by telephone. In this contact, the researcher provides additional information about the implications of participation and checks the eligibility of the employee by questions about the six exclusion criteria. If an employee meets all the selection criteria and continues to be willing to participate, written information is provided. The researchers plan a face-to-face appointment with the employee to give consent, fill in the baseline questionnaire and perform the randomisation.

### Usual occupational care in the Netherlands

The Improved Gatekeeper Act regulates, that the responsibility for RTW is given to the employer and employee together. An employer is obliged to start rehabilitation as soon as possible, in order that the employee can resume own work or other adequate work. The employee should accept the work activities the employer provides. Also, the employee has to visit the OP who can provide advice about RTW and who can guide employees on sick leave with CMDs according to the evidence-based guideline of the Dutch Association of Occupational Physicians (NVAB) published in 2000[7,24]. This guideline aims to provide an optimal functioning of the employee with an CMD to prevent long-term sick leave and frequent recurrences. The basic idea of this guideline is that recovery can only appear in interaction with the work-environment and should be based on time-contingency. It starts with the establishment of the diagnosis and a listing of the problems within the private life, the work situation and the health care system. The duration of each stage in ordinary recovery is prescribed in the guideline, hence interventions can be initiated when the OP observes that recovery stagnates.

### Description of the workplace intervention

The workplace intervention is based on a cost-effective protocol for sick-listed employees with low back pain[10,25]. This protocol is based on principles of 'participatory ergonomics' [26], however applied as a means of tertiary prevention. The process of development of this intervention for employees with CMDs is described elsewhere [9]. The workplace intervention is a stepwise and systematic approach, preceded by a consult with the OP (Figure 2). The objective of the workplace intervention is to reach consensus about an RTW plan by active participation and strong commitment of both the employee and his or her supervisor, guided by an RTW coordinator (in this study a company social worker or a labour expert). The role of the RTW coordinator does not comprise an all knowing expert who advises the employee and the supervisor about the RTW process. The RTW coordinator should provide guidance of the process to reach consensus between the employee and the supervisor about an RTW plan. The employee's and the supervisor's active participation is essential to achieve a sound basis for implementation of the RTW plan.

**Figure 2 F2:**
[figure not shown]
**Content of the workplace intervention**. The steps of the workplace intervention and the stakeholders involved.

#### Consult OP

All employees consult the OP before the intervention starts. In this consult the guidelines for usual care are followed. The OP instructs the inventory for stressors to participants as a homework assignment and, if needed, extra consults for stress reduction are planned before the intervention starts. The OP is further responsible to inform the supervisor about the workplace intervention and to ask for his or her participation. To prevent conflicting advise about RTW the OP sends a letter about the workplace intervention and a communication form to the employee's general practitioner. Like in usual care, the OP provides advice about the date of work resumption.

#### Organizational preparation

The RTW coordinator contacts the supervisor to check whether the supervisor is sufficiently informed about the intervention and agrees with it. Next, the RTW coordinator informs who is responsible for work adjustments and what procedures should be followed. The employee and supervisor are contacted by phone to plan the three meetings. If required, a checklist with questions about barriers for RTW are sent to the employee and the supervisor by the RTW coordinator. During the meetings with the employee and the supervisor the RTW coordinator emphasizes that the RTW plan does not implicate that the employee is urged to return to work immediately.

#### Inventory of barriers for RTW

The meeting of the RTW coordinator and the employee starts with a work visit, to observe the employee's workplace. The elements of work content, work environment, communication and collaboration, and work organization are discussed. This provides the RTW coordinator with a complete picture of the work situation.

Then, the RTW coordinator interviews the employee to obtain a description of the main tasks and specific features of these tasks. For each task, barriers for RTW are summarized and are judged based on the frequency and severity of the barrier. Based on this information, barriers are prioritized in order to select the most important.

Subsequently, a meeting between the RTW coordinator and the supervisor intends to select barriers for RTW of the employee from the supervisors' perspective. This procedure is the same as in the interview between the employee and the RTW coordinator. Then, the RTW coordinator summarizes the results of the two interviews and formulates the barriers to be discussed in the next meeting.

#### Thinking of solutions

After the meetings with the employee and the supervisor separately, a meeting takes place with the employee, the supervisor and the RTW coordinator to brainstorm about solutions and to draw up a plan for implementation of solutions. If agreement exist about the barriers to be solved, the RTW coordinator explains the brainstorm procedure. According to the nominal group technique [10] they think of and collect ideas for each solution. All ideas are ordered and judged based on criteria of availability, feasibility and solving capability of the solution and then prioritized. This process is repeated for each barrier. The main goal is to reach consensus between the employee and the supervisor about the most feasible solutions.

#### Preparation of the implementation

Together, the employee, the supervisor and the RTW coordinator formulate a plan for implementation of the solutions. This plan describes who is responsible for the implementation of a solution, how this is planned to occur and when the solution should be implemented. The RTW coordinator writes a report about this plan for implementation of solutions and sends it to the employee, the supervisor and the OP.

#### Implementation of solutions

In the weeks following the meetings, the solutions are implemented. If required, an RTW coordinator plans a meeting in the workplace to instruct and advise the employee at work. For instance, how to deal with a new job performance or with new equipment. At the same time, the supervisor can be informed about how to encourage and guide the employee in his or her (adjusted) work situation.

#### Evaluation by the RTW coordinator and follow-up by the OP

One month after the meetings, the RTW coordinator contacts the employee and the supervisor to inform whether the solutions have been implemented successfully and whether this has contributed to RTW. The RTW coordinator draws up a final report, describing the process and outcome of the implementation and assigns further guidance to the OP.

### Training health care professionals

All OPs involved in this study were trained half a day in the referral of employees to the workplace intervention and the researchers informed them how the workplace intervention is embedded in the guideline for OPs. The referral for the workplace intervention is in line with the guidelines, although explanation about the workplace intervention and standard explanation of the inventory of stressors to the employee is additional. RTW coordinators followed a one-day training course including several role-playings. Each RTW coordinator who guides a first case according to the protocol was contacted by the researchers to facilitate the process. Two follow-up training sessions were conducted during the recruitment period to discuss difficulties and to practise with cases.

### Sample size

Time to lasting RTW is the primary outcome measure for the power calculation. In order to calculate the sample size we assumed that a Hazard Ratio (HR) of 2.0 is the smallest clinical and societal relevant ratio. A HR of 2.0 indicates that employees in the intervention group return to work twice as quickly as employees in the control group. This HR is based on recent studies in occupational health care on RTW of short-term sick-listed employees with low back pain and adjustment disorders[11,25,27,28]. Assuming that a minimum of 2/3 of the participants achieve a full RTW during the follow-up, the calculation showed that a sample size of 98 employees is needed (a power of (1-β =) 0.80 and a two-sided significance level of 0.05 (α)). Since the OPs, because of their role and function in the RTW process, may influence the RTW date, a multilevel analysis on the level of the OP is taken into account. For 13 OPs and an intraclass correlation coefficient (ICC) of 0.05 (clustering in our groups is not presumed to be large) a total of 130 employees are needed. When taking into account a loss to follow-up of 10%, 144 employees have to be enrolled in the study. Although loss to follow-up is taken into account, we do not expect a high loss to follow-up in this study because data about the primary outcome (lasting RTW) will be acquired from the continuous company registration systems after the one-year follow-up.

### Randomisation procedure

An independent statistician prepared the randomisation by using a computer-generated randomisation. To prevent unequal randomisation, employees are pre-stratified by company and whether they are on full or part-time sick leave. Furthermore, block randomisation (with blocks of four) is applied to ensure equal group sizes within each stratum. The researchers prepared sealed envelopes before the start of the study containing either a referral to the workplace intervention group or the usual care group. If the baseline questionnaire is completed, each employee can choose one of the two succeeding envelopes of the correct stratum provided by the researcher. The employee is asked to open the envelope and write down his or her name and the date on the note that contains the randomisation result.

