### Blinding

The participants, the occupational health professionals and the researcher are not blinded for the group assignment. It is likely that several participants of one department will participate and therefore knowledge about both groups is provided for the participants. Furthermore, OPs will be visited by both employees in the workplace intervention group and employees in the usual care group. Therefore they cannot be blinded. Since all follow-up questionnaires are sent to the employee by mail, no direct influence by the researchers or occupational health professionals is likely to occur.

The registration of sick leave in the Netherlands is done by companies and managed by the occupational health services. Since these measurements are extracted from computerized databases, bias caused by a lack of blinding is prevented for this outcome. Since the secondary outcomes are all self-reported, blinding is impossible. After randomisation all participants receive a research code consisting of a consecutive number. A research assistant will put all data in the computer by the research code. Therefore, the analysis of the data by the researcher will be blind.

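### Unblinded researchers both prepare the envelopes and enrol, with fixed blocks of four, so the next allocation can be guessed about 68% of the time; the two-envelope choice does not cure this and loosens the blocking slightly

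*Protocol article*

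**What the plan says.** All references are to the protocol article.

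- **Sequence.** Under Randomisation procedure, "An independent statistician prepared the randomisation by using a computer-generated randomisation".
- **Envelopes.** The same section continues: "The researchers prepared sealed envelopes before the start of the study".
- **Strata and blocks.** In that section "employees are pre-stratified by company and whether they are on full or part-time sick leave", and "block randomisation (with blocks of four) is applied to ensure equal group sizes within each stratum".
- **Draw.** Once the baseline questionnaire is complete, "each employee can choose one of the two succeeding envelopes of the correct stratum provided by the researcher". The employee opens the envelope and writes name and date on the note inside.
- **Enrolment.** Under Recruitment of study population, the researcher telephones willing employees and "checks the eligibility of the employee by questions about the six exclusion criteria". Then: "The researchers plan a face-to-face appointment with the employee to give consent, fill in the baseline questionnaire and perform the randomisation".
- **Blinding.** "The participants, the occupational health professionals and the researcher are not blinded for the group assignment".
- **Claimed protection.** Methodological considerations says that selection bias is limited because the occupational physician (OP) has no part in inclusion, and concedes possible self-selection by employees. It does not discuss the researcher.

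**The concern.** Concealment requires that whoever decides on entry cannot foresee the next assignment. Here the statistician's independence covers the making of the list. It does not extend to the envelopes, which pass through the hands of the group that enrols. That group sees each result, and it knows an employee's company and full or part-time sick-leave status, hence the stratum. A fixed block of four makes past results informative about the next one.

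If the next assignment can be anticipated, it can influence how an eligibility answer is read, how warmly an employee is encouraged, or who is given the next appointment. The arms would then differ in prognosis from the start. Intention-to-treat analysis does not repair this, and adjustment for baseline differences deals only with what was measured. Registry-based outcomes and coded data entry protect assessment and analysis, not entry.

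A second, smaller matter is that offering two envelopes means the list is not followed in order, although the blocks are there to give equal groups within each stratum.

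**Working it through.** The article gives no figure for predictability or balance, so there is none to reproduce.

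**Inputs from the article:** blocks of four; two arms of equal size; choice of one of the next two envelopes in the stratum; 144 employees to be enrolled (Sample size).

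**Assumptions, not in the article:** the enroller knows past results in the stratum; picks are 50:50; the unchosen envelope is offered again with the next one. For illustration there are four equal strata, 144/4 = 36 employees each.

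**1. Benchmark: envelopes opened in strict order.** There are six possible blocks with two of each arm.
- Chance of a correct best guess by position: first 1/2; second 2/3; third (1/3)(1) + (2/3)(1/2) = 2/3; fourth 1.
- Mean: (1/2 + 2/3 + 2/3 + 1)/4 = 17/24 = 70.8%.
- Certain in advance: (1/3 + 1)/4 = 33.3%.

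**2. The procedure described: one of two, unchosen envelope carried forward.** Simulated strata of 36, with the enroller's probabilities updated exactly after each result:

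| | Certain | Best guess correct |
|---|---|---|
| List continues beyond 36 | 9.8% | 68.1% |
| List ends at 36 | 12.6% | 68.8% |

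The gap in certainty is essentially the last envelope in a closed list, which leaves no choice: 1/36 = 2.8 percentage points. The choice thus cuts certainty from 33% to 10–13% but lowers the guess rate only from 71% to 68–69%.

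**3. If the contents of both offered envelopes were known.** They match 40.8% of the time, so that share is certain. Otherwise the employee's pick is a coin toss: 40.8% + 59.2%/2 = 70.4% guessed correctly.

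**4. Balance, unchosen envelope carried forward.** After 4m employees, 4m + 1 envelopes have come into play and one is left over.
- The first 4m envelopes balance exactly, so the arm difference equals envelope 4m + 1 minus the leftover (coding the arms +1 and −1). It is therefore 0 or 2.
- With probability 1/2 the leftover is envelope 4m + 1 itself, giving 0. Otherwise it is an older envelope, of the opposite arm half the time. The chance of inequality is 1/2 × 1/2 = 25%, against 0% in strict order.
- If the list ends at 36, the ninth block end must balance, giving 8/9 × 25% = 22%.
- The final difference is at most 2. The running difference can reach 3, against 2 in order.

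**5. Balance, if unchosen envelopes were discarded.** Each block then supplies two employees. Two assignments in a block of four have covariance −1/3, so the variance of their sum is 2 − 2/3 = 4/3.
- For 36 employees (18 blocks): 18 × 4/3 = 24, standard deviation 4.90, mean absolute difference about 0.80 × 4.90 = 3.9. Simulation agrees, with a 95th percentile of 10.
- Simple randomisation: standard deviation 6, mean about 4.8.

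**The case against.** Much can be said for the plan. Candidates come from occupational health databases through a mailed screener with a distress cut-off and the employee's own statement of willingness. Most exclusion criteria are factual, such as hours worked, pregnancy and weeks on sick leave. The envelope is drawn only after consent and baseline, the employee makes the pick, and the note is signed and dated. The article does not say that the researcher reads the expected duration of absence before inviting or randomising. All of this stands. It narrows the room for influence but leaves the telephone call, the encouragement and the appointment order, which all come before the draw.

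A reader might infer more than the text supports:

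- **That the researchers held the list and knew every assignment.** The article does not say who held the list, or that the individuals who filled the envelopes also enrol. Even with both contents known, the employee's pick leaves about 59% of assignments uncertain.
- **That a third of assignments are known in advance.** That figure belongs to opening in strict order, which this trial does not do.
- **That the two-envelope choice makes assignments easier to foresee.** It lowers certainty. Its own cost is to the blocking, and that is small if envelopes are carried forward.
- **That the blocking is lost.** This would need unchosen envelopes to be discarded. The text does not say so, and its wording fits carrying them forward at least as well.

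It is also fair that the article uses the past tense for consent and for training during recruitment, so few allocations may remain to be changed.

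**Conclusion.** The weakness lies in stated procedure, not in detail that a condensed article leaves out. Unblinded researchers prepare the envelopes and run entry, and the block size is fixed and small. Under the procedure as described, an enroller who merely keeps track can guess about 68% of assignments against 50% by chance, and is certain of about 10–13%. That result does not need the envelope fillers and the enrollers to be the same people. It does need the enroller to know past results in the stratum, and it rests on carry-forward and 50:50 picks.

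The effect on balance is modest: a difference of 2 at 22–25% of block ends and at most 2 at the end. Only under discarding would a stratum of an assumed 36 come near simple randomisation (mean difference about 3.9 against 4.8).

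Nothing shows that allocation was subverted, and the sample size is unaffected. The statement under Methodological considerations is too narrow, because it covers the OP and not the researcher who enrols. The change is worth making because it is cheap, not because bias has been shown.

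**What to change.** **If allocations remain:**
- Have the independent statistician, or another person who does not enrol, prepare and hold opaque, sequentially numbered envelopes, or release each allocation remotely.
- Vary the block size at random and do not disclose the sizes to the researchers.
- Use only the next number in the stratum, after eligibility, consent and baseline are recorded. Drop the choice between two envelopes.

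**If recruitment is complete:** report who filled the envelopes and whether they also enrolled, how unchosen envelopes were handled, and baseline prognosis by arm.

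**In either case:** qualify the selection-bias statement under Methodological considerations so that it covers the researcher's role.

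**Cost:** a small procedural amendment, a little time from the statistician already engaged, and a slightly larger possible imbalance within strata from varied blocks. Reporting alone costs a few sentences and a baseline table.
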